## Abstract

**Background:**

Preterm birth (PTB) is a leading cause of neonatal morbidity and mortality. More than 13 million babies are affected globally every year and PTB will contribute to over 900,000 deaths. In the UK, PTB affects 8% of pregnancies and costs more than £260 million annually in neonatal care. Identifying those at risk of this devastating complication of pregnancy and implementing preventative treatment remains a maternal health priority. The mainstay of PTB prevention has been assessment of cervical length (CL) in women at high-risk of PTB. However, CL has limitations, namely it is invasive, user dependent and varies over time through pregnancy. Importantly, not all those who are high-risk with a short CL will subsequently deliver preterm and CL screening doesn’t identify a sub-set of women who have a spontaneous PTB without a short cervix. Therefore, existing care pathways for managing PTB can potentially benefit from additional assessments of risk. Novel ways of assessing cervical structure and function may improve our ability to predict spontaneous PTB and refine preventative intervention. This feasibility study will explore the use of a new antenatal test of cervical stiffness for assessing risk of spontaneous PTB in a high-risk singleton population.

**Methods:**

PRECISION is a single site prospective, feasibility, cohort study of asymptomatic women with singleton pregnancies at high risk for spontaneous PTB attending an inner-city tertiary maternity hospital in the UK. All study participants will be undergoing routine screening and management of PTB as per local guidance (NICE/Saving Babies Lives guidance) including CL screening with transvaginal ultrasound. Cervical stiffness will be assessed using the Pregnolia System; a novel, licensed, CE-marked, aspiration-based device. A measurement is obtained by applying the device directly to the anterior lip of the cervix, visualised via placement of a speculum, and gives a quantitative assessment of cervical stiffness represented as the Cervical Stiffness Index (CSI, in mbar). Participants will undergo cervical stiffness assessments at up to three timepoints in the second trimester between 14^+0^ weeks and 25^+6^ weeks gestation. The cervical stiffness index data will be paired with routine PTB clinic CL measurements taken at the same time points. The primary outcome will focus on the feasibility of using this novel antenatal test in this high-risk population and explore any association between cervical stiffness and PTB.

**Discussion:**

This is an exploratory study to assess the use of this novel device in clinical practice. Direct comparison between cervical stiffness assessment using the Pregnolia System and CL assessment will determine the acceptability of this new assessment in this population, as well as explore its potential association with PTB. Our findings from this feasibility study will provide data on the potential of this novel device to impact PTB screening and evaluate acceptability of use in a high-risk population. Data on eligibility, recruitment rates and participant feedback will help inform future study design using the device.

**Trial registration:**

ClinicalTrials.gov NCT05837390

## Introduction

Preterm Birth (PTB), defined as delivery at less than 37 + 0 weeks gestation, is the single biggest cause of neonatal mortality and morbidity in the UK. Unfortunately it remains a common complication of pregnancy involving around 8% of births in England and Wales and affecting over 52,000 babies annually [1]. With increased surveillance, and intervention targeted towards preventing and managing PTB, mortality at extreme preterm gestations has improved. However, babies who survive PTB and are born at the earliest gestations suffer the greatest consequences of neurodevelopmental disability. Overall, the UK PTB rate has not declined over the last 10 years and the need for innovative evidence-based policy for PTB risk stratification remains a clinical priority [1–3].

Understanding the events leading to spontaneous PTB remains a significant research challenge due to its’ complex and multifactorial aetiology [4,5]. Despite advances in PTB prediction and prevention a large proportion of spontaneous PTB remains undetected prior to the onset of labour or remains intractable to current interventions [4]. More than half of PTBs occur in women with no known or identifiable risk factors [6]. This reiterates the importance of developing novel approaches to predicting PTB.

Previous history of PTB is the strongest predictor of subsequent PTB and is used to define women as “high-risk” for PTB [7,8]. Transvaginal cervical length (CL) ultrasound assessment is widely accepted as the preferred screening tool used for predicting PTB in asymptomatic high-risk women [7,9]. These two findings form the basis of current PTB risk stratification in the UK through dedicated PTB clinics that perform surveillance second trimester CL scans on high-risk pregnant women. However, limitations exist with CL as a screening tool, and it remains unable to accurately predict all high risk women who will go on to have a spontaneous preterm birth < 34 weeks [10].

Premature cervical shortening precedes the onset of spontaneous PTB [7]. This is just one parameter of cervical remodelling that can be measured, as the cervix also needs to soften and dilate prior to spontaneous delivery [11]. Research into other bio-mechanical properties of the cervix and its relationship to PTB have included cervical consistency and stiffness assessments using advanced ultrasound imaging techniques and mechanical tissue tests [4,6,12–15]. Importantly, it has been identified that the cervix softens before it shortens [13]. Pathological cervical remodelling can be detected earlier in asymptomatic individuals and with better diagnostic performance when measuring cervical stiffness compared to length for PTB prediction [13,16–18]. However, application of these proposed cervical consistency assessment tools relies upon expert ultrasound skills using expensive resources. So far, no objective technique to assess cervical softness during pregnancy has been well established in clinical practice [16,19].

The Pregnolia System is a CE-certified, novel device that provides objective, quantitative assessment of cervical stiffness through an aspiration-based technique [19,20]. Initial studies in a low-risk, unselected population have confirmed the device can detect cervical softening at an earlier gestation than ultrasound can detect cervical shortening, demonstrating its’ potential use for PTB prediction [21]. Further studies have echoed this potential with findings of significant cervical softening in populations already identified as requiring intervention to prevent PTB [22,23]. So far, there has been no published evidence of using cervical stiffness (CSI, mbar) obtained with the Pregnolia System as a risk biomarker for PTB in an asymptomatic high-risk population. A feasibility study is needed to investigate the acceptability, implementation and efficacy of the Pregnolia System for cervical stiffness in the representative high-risk population to justify a further large scale predictive study and inform its appropriate design and power [24].

This feasibility study aims to confirm whether a lower cervical stiffness result obtained using the Pregnolia System has an association with spontaneous PTB in high-risk singleton pregnancies [25]. The study will also directly compare the current gold standard practice of serial CL surveillance in the second trimester to paired cervical stiffness assessments [1]. This study will explore how this device and its’ results can be applied to the population served by the PTB clinic and review acceptability of this assessment in these patients. Together, these results will help inform a future study using the Pregnolia System as a potential predictive tool for PTB.

## Materials & methods

### Study design

This study is a single site prospective, observational, cohort study taking place at the Liverpool Women’s Hospital in the UK. Participants will be recruited directly from the Preterm Birth Clinic (PTBC) at this tertiary women’s hospital between 14^+0−^25^+6^-weeks’ gestation.

Participants will undergo cervical stiffness assessment using the Pregnolia System up to three times during their PTB surveillance14^+0^ to 25^+6^ weeks gestation at study time points outlined in Fig 1. The CSI measurements will be undertaken alongside their CL scan measurements as part of their routine PTBC care [3].

**Fig 1 pone.0316297.g001:**
[figure not shown]
Study Flow Chart.

Participants will complete a structured questionnaire after their first clinical examination in the study. This questionnaire will collect patient experience of the cervical stiffness assessment in comparison to standard CL assessment and collate data as to the acceptability of the assessment in this patient population (supporting information S1 Fig). Participants attending at Study Visit A time point will be invited to consent to gifting two high vaginal swabs as samples for future vaginal-microbiome research. These gifted samples will be obtained during the speculum procedure used for cervical stiffness assessment.

All study participation will coincide with the participants routine PTBC appointments, and participants will continue to receive all PTB intervention and surveillance as guided by their clinicians and as per national and regional PTB guidance (SBLCBV3, NICE Preterm Labour and Birth guidelines and the North West Regional network PTB guideline) [1,3,26]. Study procedures at each visit are detailed and explained in the study flow chart (Fig 1).

In this feasibility study we will recruit patients for 15 months and expect to achieve a cohort of 60 patients based upon expected high-risk clinic referrals and an assumed recruitment rate of 40%.

Participants will remain in the study following recruitment until delivery and discharge from hospital. Study outcomes will be collected from electronic hospital records for the participant and their baby.

## Study objective

The PRECISION study has the following objectives

To obtain cervical stiffness measurements during the second trimester in high-risk singleton participants to:Determine the reliability and best interpretation of triplicate measurements in this patient group at this gestation.Explore any potential association between second trimester cervical stiffness and gestation at delivery.Compare cervical stiffness assessments to CL measurements taken concurrently and explore the association with gestation at delivery.•To explore the acceptability of this assessment tool in this patient population for PTBC screening.•Upon positive conclusion of the PRECISION feasibility study, to inform for the design of an appropriately powered study to assess the capability of this novel device for PTB prediction.

## Study population

The PRECISION study population will consist of consecutive pregnant women attending the PTBC at Liverpool Women’s Hospital. Study eligibility will be determined at their initial attendance at the PTBC by the clinical team. Patient’s meeting the inclusion and exclusion criteria, who wish to take part in the study must provide written informed consent for study procedures and use of their data from electronic medical records.

### Inclusion and exclusion criteria

All participants should meet the following inclusion criteria to be eligible:

Age ≥  18 yearsSingleton pregnancyAble to provide informed consentMeets criteria for high-risk PTBC, either:Previous preterm prelabour rupture of membranes (PPROM) < 34 + 0 weeksPrevious PTB ≥ 16 + 0 to < 34 + 0 weeks.

Any possible exclusion criteria will be evaluated for eligibility for the study on the first visit and includes:

Previous cervical surgery including previous trachelectomy, cone biopsy, loop excision or previous cerclageExisting cervical cerclage (vaginal or abdominal)Known cervical pathology at 12 o’clock position (cervical scarring due to prior large loop excision of the transformation zone (LLETZ) or cone biopsy/Nabothian cyst/polyp/cervical tears/cervical myomas/cervical condylomas/cervical endometriosis/cervical cancer)Vaginal bleeding evident on examinationVisible, symptomatic cervical or vaginal infectionsSymptomatic of PTB (ruptured membranes, cervical dilatation, painful regular contractions)Known congenital uterine anomaliesKnown or suspected structural/chromosomal fetal abnormalityKnown HIV infection

## Study procedures

### Pregnolia System

The Pregnolia System is a novel medical device designed to quantitatively assess the biomechanical properties of the cervix through cervical stiffness. The system consists of a single-use sterile probe and a control unit as seen in Fig 2. The control unit is the active component that requires a power supply, foot switch for clinician control, and an integrated pump that generates a vacuum. The sterile probe is attached to the control device via a connector cable and air filters on the probe prevent microbiological contamination [27].

**Fig 2 pone.0316297.g002:**
[figure not shown]
Pregnolia System-Control Unit with foot switch and single-use sterile probe.

The device requires the use of a vaginal speculum to clearly visualise the cervix. The device probe is placed at the 12 o’clock position on the cervix and the cervical stiffness measurement is operated by a foot switch, creating a weak vacuum which displaces the cervical tissue into the probe tip to a depth of 4mm. The softer the tissue, the less pressure required to deform the tissue [28]. The result is represented by the CSI shown on the control unit. The Pregnolia system provides audio guidance to the clinician by indicating that the measurement has started, is in progress and is complete.

The device has clear operation instructions for use that outline appropriate clinical indications and contra-indications for use. All clinicians using the device will have read the instructions and completed the Pregnolia training instructional video.

### Cervical stiffness assessment

Cervical stiffness will be measured using the Pregnolia System. Following informed consent, all measurements will be performed with the woman in a supine position with an empty bladder. A vaginal speculum will be placed to visualise the cervix and the single-use, sterile Pregnolia Probe is placed on the anterior lip of the cervix at 12 o’clock position. A recording of cervical stiffness is generated over a maximum of 60 seconds (typically ~15 seconds) and displayed as CSI in mbar. The measurement is repeated 3 consecutive times without any time lag. The clinician is audio-guided by the control unit which indicates when a reading has been taken.

The cervical stiffness readings will be stored on the Pregnolia Control Unit and only documented for the participant once all study procedures have been completed during that study visit. The cervical stiffness readings are blinded to the patient and the clinician at the time of the study visit.

Any difficulty in obtaining readings will be documented on the case report form (CRF). Simple troubleshooting guidelines will be followed to optimize readings at the time of the study visit as per Pregnolia Instructions (e.g., avoiding kinks in connector cable and ensuring Luer locks are secure).

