### Feasibility outcomes

Our feasibility outcomes of interest relate to whether the study procedure is acceptable, participant adherence and retention to the study is achieved, data collection is feasible, and that cervical stiffness assessment fidelity is maintained with adequate reliability and safety[34].

Our feasibility outcomes will be defined as follows;

1)Participant acceptability of cervical stiffness assessment in PTB clinica.Qualitative questionnaire following assessmentb.Number of participant withdrawals throughout the study duration (aim for < 20%)c.Reasons for non-participation collected of eligible women approached for the study2)Adherence to the protocola.Measured as number of protocol deviations3)Adherence to data collectiona.Numbers of missing data (aim for < 10%).b.Loss to short term follow up (aim for < 5%)4)Safety outcomesa.Incidence of adverse events5)Cervical stiffness fidelitya.Ability to obtain triplicate cervical stiffness measurements (aim for > 90%)b.Triplicate measurement reliability (aim for > 0.8 Cronbach’s Alpha)6)Inputs for sample size and power calculation of future studya.Determine sPTB rate in the total study population (participating and non-participating PTBC patients) to inform current sPTB rate post national guidance care implementationb.Determine estimate of CSI variance using the Pregnolia Systemc.Determine recruitment rate to the study to inform sample size required

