### Statistical analysis

Descriptive statistics will be generated and presented as means (SD), median (IQR) and frequency of observations (percentages) with 95% confidence intervals as appropriate.

Cronbach’s Alpha will be used to assess the reliability of the device to produce consistent readings at different time points. It compares shared variability among the measurements with the overall variance. If the device is reliable then there should be high covariance amongst the measurements relative to the variance. Cronbach’s alpha alongside descriptive statistics with 95% confidence intervals will inform best use of the triplicate CSI measurements taken at each study visit. Specifically exploring whether the first, average, median or lowest measurement of the three readings should be utilised in further analysis and most importantly inform best use of the CSI results in clinical practice.

An estimate of the variability in the outcome measure will be calculated and then applied to a sample size calculation for a further definitive study.

Diagnostic performance of cervical stiffness assessments using the Pregnolia System for PTB will be demonstrated through receiver operating characteristic curves with area under the curve and 95% confidence intervals being calculated, as well as aiming to define the optimum cut-off value for predicting PTB. Cervical length diagnostic performance data will also be generated for direct comparison.

Any association between cervical stiffness and gestational age at delivery will be explored using scatter plots and linear regression. Longitudinal data will be explored using time series plots, and box plots with a sensitivity analysis completed on all participants with a complete data set.

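### Alpha above 0.8 on three back-to-back readings shows repeatability within one examination only; it cannot detect user dependence and, with several operators, may be raised by it

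*Protocol article*

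**What the plan says.** All references are to the protocol article.

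- **How the readings are taken** (Cervical stiffness assessment): "The measurement is repeated 3 consecutive times without any time lag". The same section speaks of one clinician: "The clinician is audio-guided by the control unit which indicates when a reading has been taken".
- **Who takes them** (Pregnolia System, text after Fig 2): "All clinicians using the device will have read the instructions and completed the Pregnolia training instructional video". The plural implies more than one operator. No number is given.
- **The criterion** (Feasibility outcomes, item 5b): "Triplicate measurement reliability (aim for > 0.8 Cronbach’s Alpha".
- **How it is interpreted** (Statistical analysis): "Cronbach’s Alpha will be used to assess the reliability of the device to produce consistent readings at different time points", with the rule "If the device is reliable then there should be high covariance amongst the measurements relative to the variance".
- **What depends on it**: alpha helps to decide how the three readings are summarised and used in practice (Statistical analysis). The CSI variance goes into the sample size of the next study (Feasibility outcomes, item 6b).
- **Why users matter** (Abstract, Background): "CL has limitations, namely it is invasive, user dependent and varies over time through pregnancy".

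The article describes no second operator, no repeat examination within a visit and no operator term in the analysis.

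**The concern.** Alpha treats whatever a woman's three readings have in common as signal. In a no-lag triplicate from one examination, that includes her true cervical stiffness and also anything fixed for that examination: speculum exposure, probe angle, and the habits of the person holding the probe. Under the article's own rule, this shared part adds to the covariance among readings and so counts as evidence of a reliable device.

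Two things follow. First, the design supports a statement about repeatability within an examination, whereas the Statistical analysis section words it as reliability of the device at different time points. Second, if operators differ from one another, alpha goes up while agreement between users goes down. Criterion 5b therefore cannot detect user dependence and may reward it. This matters because user dependence is one of the faults of cervical length that the article gives as a reason for studying the new device.

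**Working it through.** **Reproducing the plan's figure.** The 0.8 is a target with no inputs behind it, so there is nothing to reproduce.

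**Inputs.** From the article: three readings per examination, target 0.8, planned cohort 60. Assumed, because the article gives no variance components: woman variance W = 1.0, repeat-error variance E = 0.9, operator variance O = 0, 0.25 or 0.5. It is also assumed that one operator takes all three of a woman's readings.

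**Formulas.** Reading = woman + operator (shared by the triplicate) + repeat error.

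- Alpha for three readings = (W + O) / (W + O + E/3)
- Reliability of the triplicate mean across operators = W / (W + O + E/3)

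**Limiting case (many operators), E/3 = 0.3.**

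| O | Alpha | Across operators |
|---|---|---|
| 0 | 1.00/1.30 = 0.769 | 1.00/1.30 = 0.769 |
| 0.25 | 1.25/1.55 = 0.806 | 1.00/1.55 = 0.645 |
| 0.5 | 1.50/1.80 = 0.833 | 1.00/1.80 = 0.556 |

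The two columns move in opposite directions. That direction does not depend on the assumed values.

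**Few operators.** The table in effect gives each woman her own operator. With K operators sharing the clinic, the expected realised operator variance is about O(1 − 1/K). For O = 0.25 that is 0.125 with two operators and 0.1875 with four. Simulation with 60 women, W = 1.0, E = 0.9:

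| Operators | O | Mean alpha | Chance of alpha > 0.8 |
|---|---|---|---|
| any number | 0 | 0.76 | about 25% |
| 1 | 0.25 | 0.76 | about 25% |
| 2 | 0.25 | 0.78 | about 39% |
| 4 | 0.25 | 0.79 | about 46% |
| 8 | 0.25 | just under 0.80 | about 50% |

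At O = 0.25 the mean stays below 0.8 throughout. At O = 0.5 two operators still average 0.79, and three or more average above 0.80. With one operator nothing is inflated, because a constant shift does not alter alpha.

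**Dependence on the starting point.** In the limiting case alpha reaches 0.8 when E/3 = (1 + O)/4. So O = 0.25 changes the verdict only if alpha without operator differences lies between 1/(1 + 0.3125) = 0.762 and 0.80. For O = 0.5 the lower limit is 1/(1 + 0.375) = 0.727. Starting lower, at an alpha of 0.70 without operator differences, the simulated chance of exceeding 0.8 is about 3% with no operator variance. With four operators it is 11%, 24% and 44% for O = 0.25, 0.5 and 1.

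**The cause is the shared examination.** If each of a woman's three readings came from a different operator (six operators, starting alpha 0.70, O = 0.5), mean simulated alpha would fall from 0.69 to 0.60. Operator differences lower alpha when they fall within the triplicate and raise it when they are shared by it.

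**The case against.** - **The premise is inferred.** More than one operator rests on a plural in a training sentence, and one operator per triplicate on a singular. This stands: the inflation is conditional. With a single operator it disappears, although alpha would still say nothing about other users.
- **The size is easily overstated.** A reader might infer from the limiting formula that an operator variance of 0.25 turns a missed target (0.769) into a met one (0.806). With two to eight operators the average does not cross 0.8. That example also starts close to the threshold, and nothing in the article supports any particular operator variance. This stands.
- **The criterion is already narrow.** Item 5b is labelled as triplicate reliability, and one use of alpha is to choose among summaries of the three readings, which is a within-examination question. The phrase about time points may mean only that alpha is computed at each visit. That is fair, but the same section still reads high covariance as a reliable device, and an alpha per visit does not measure agreement between visits.
- **Operator identity may be recorded.** The case report form is not shown, so a reader should not infer that operator goes unrecorded. This stands. The point is the inference drawn from alpha, not a missing form field.
- **Item 6b is not wrong.** A reader might infer that operator variance contaminates the CSI variance. A later study with ordinary clinic staff needs the total variance, operator part included, and dropping that part would risk underpowering it. This stands. Showing the components beside the total adds information and corrects no error.

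**Conclusion.** The point holds in a limited form. Alpha above 0.8 on this triplicate supports short-term repeatability within one examination. It does not support reliability across time points or across users, and the Statistical analysis section reads more into it than the design can give. If more than one clinician measures and they differ, alpha is raised by that difference.

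The direction is certain under that condition; the size is not known. On the assumed variances (1.0, 0.9, 0.25; 60 women; two to eight operators) mean alpha rises by about 0.02 to 0.03, and the chance of meeting the target goes from about one in four to between 39% and 50%. The documents do not support the stronger conclusions that the target will be met because of operator differences, or that the study sets out to prove user independence and fails.

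**What to change.** 1. In Feasibility outcomes 5b and in Statistical analysis, describe the alpha target as within-examination repeatability. State that no conclusion on reliability across users or time points will be drawn from alpha alone.
2. Use a coded operator identifier for every CSI examination, adding it to the case report form if it is not already there.
3. For 6b, keep the total CSI variance as the sample-size input. Beside it, report woman, operator and residual components with intervals, from a mixed model with gestation over the up to three visits per woman. If individual readings are modelled rather than one value per examination, include an examination term.
4. Do not replace alpha by a version with operator means removed. Operators are not said to be randomly allocated, so this could strip out true between-woman variance and understate repeatability.

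**Cost:** some rewording, at most one form field, and one model. No extra examination is needed. **Downside:** with few operators the operator component will be imprecise, and without random allocation it may be confounded with case mix. It should be reported as descriptive.

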### Cervical length assessment

Clinical staff will perform transvaginal ultrasound assessment of CL using a GE Voluson E10 ultrasound machine and 7.5MHz transvaginal probe. All measurements will be performed with the woman in a supine position with an empty bladder in the sagittal plane measuring from the internal to external cervical OS. The full length of the cervical canal will be visualized with the closed portion of cervix remaining being measured in triplicate.

The shortest CL measurement of the three readings will be documented as the final CL measurement for that study visit. CL measurements will be known to both the participant and clinician at the time of assessment and will be used to guide ongoing surveillance and PTB intervention as per the clinical team decision-making and regional guidelines.

The study procedure order is further outlined in the study flow chart (Fig 1) and schedule of study procedures (Table 1). Participants will remain in the study for a maximum of 31 weeks, from initial visit to PTBC until point of discharge after delivery, or infant aged 1 month. Assessments will take place at specified timepoints as shown in the study schedule (Table 1).

**Table 1 pone.0316297.t001:** Schedule of Study Procedures.

Order of Procedures	At PTBC triage (12 weeks)	Study Visit A (14+0−17 + 6 weeks)	Study Visit B (18 + 0−21 + 6 weeks)	Study Visit C (22 + 0−25 + 6 weeks)	Postnatal & End of study
*Patient Eligibility*	**X**				
*Patient information Leaflet provided*	**X**				
*Informed Consent*		**X**			
*Pre-Sample Collection Questionnaire*		**X**			
*High Vaginal Swab Collection (2 gifted samples)* * *optional*		**X**			
*Cervical Stiffness Measurement*		**X**	**X**	**X**	
*Cervical Length Scan*		**X**	**X**	**X**	
*Post-Assessment Patient Questionnaire*		**X**			
*Delivery Outcomes*					**X**
*Maternal Postnatal Outcomes*					**X**
*Neonatal Postnatal Outcomes*					**X**
*Adverse Event Reporting*		**X**	**X**	**X**	**X**

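### CSI is masked only during each study visit, so earlier readings could be known at later CL scans, in clinician-guided care and when a birth is classified

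*Protocol article*

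**What the plan says.** The masking rule is in the protocol article under Cervical stiffness assessment: "The cervical stiffness readings are blinded to the patient and the clinician at the time of the study visit". The sentence before it says that readings are stored on the control unit and "only documented for the participant once all study procedures have been completed during that study visit".

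Under Study design, "Participants will undergo cervical stiffness assessment using the Pregnolia System up to three times", and Table 1 places these visits at 14+0 to 17+6, 18+0 to 21+6 and 22+0 to 25+6 weeks. CL is handled openly (Cervical length assessment): "CL measurements will be known to both the participant and clinician at the time of assessment and will be used to guide ongoing surveillance". Care stays with the clinic (Study design, text after Fig 1): "participants will continue to receive all PTB intervention and surveillance as guided by their clinicians".

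The CSI data then serve an objective, "Explore any potential association between second trimester cervical stiffness and gestation at delivery", and a ROC analysis "aiming to define the optimum cut-off value for predicting PTB", with CL analysed alongside for direct comparison (Statistical analysis).

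**The concern.** The article states when masking applies, and that period ends too early for the analyses planned. Masking within a visit can protect that visit's CL scan, because Table 1 lists the stiffness measurement before the scan. It gives no protection after the visit, and that is when further CL scans, decisions on surveillance and intervention, and the birth itself take place.

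If a known low CSI led to extra effective care, some of the births it would have predicted would not happen and CSI would look weaker than it is. If it coloured a later CL measurement, the comparison of the two tests would no longer be between independent readings. If it affected how a birth came about or was classed, the event count could move in either direction. None of this would be visible in the results, and the cut-off and association are meant to inform a larger study.

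**Working it through.** The article gives no figure on this point, so there is nothing to reproduce. The check is mainly a reading of the text, followed by an illustration on assumed values.

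**1. How long the unmasked period can be.** For a woman measured at Visit A (14+0 to 17+6 weeks), the time from that visit to the 34+0 week threshold of the primary clinical outcome runs from 34+0 − 17+6 = 238 − 125 = 113 days (16 weeks 1 day) to 34+0 − 14+0 = 238 − 98 = 140 days (20 weeks). The stated rule masks her CSI only during the visits themselves.

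**2. What falls in that period.**
- Up to two further CL scans (Visits B and C), performed by clinical staff.
- Surveillance and intervention, which follow clinical team decisions as well as guidelines, so judgement has a part.
- The outcome. Clinical outcomes counts labour with intact membranes or preterm prelabour rupture of membranes (PPROM), and excludes induction without PPROM and elective caesarean. A delivery decision can therefore determine whether a birth is an event.

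**3. What the article does not say.** No section withholds Visit A or B readings from the treating team later on, or says that CSI must not influence care. Equally, no section says that the readings are released to the team or used.

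**4. Conditions for bias.** Three things must all happen: someone in the care or classification pathway learns the CSI; that person acts on it; and the action changes a CL measurement, a delivery or a classification. If any one fails, the bias is zero.

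**5. Illustration of the treatment route only.** The document supplies 60 women. Everything else is assumed: an 18% event rate (the site's historical figure, which the article itself says cannot be extrapolated), a true AUC of 0.70 or 0.80, and extra effective care for a share of the softest quartile.
- Expected events without leakage: 60 × 0.18 = 10.8.
- Binormal model with separation d = √2 × z(AUC), 1,000,000 simulated women.
- Each event in the softest quartile is averted with probability share × (1 − RR). With shares of 25% to 100% and RR of 0.8 to 0.6, this runs from 0.25 × 0.2 = 0.05 to 1.0 × 0.4 = 0.40.
- 95% half-width = 1.96 × the Hanley-McNeil standard error at N = 60.

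| Scenario | AUC | Expected events | 95% half-width |
|---|---|---|---|
| True AUC 0.70, no leakage | 0.702 | 10.8 | 0.187 |
| Share 25%, RR 0.8 | 0.694 | 10.6 | 0.190 |
| Share 100%, RR 0.6 | 0.633 | 8.8 | 0.211 |
| True AUC 0.80, no leakage | 0.800 | 10.8 | 0.167 |
| Share 25%, RR 0.8 | 0.792 | 10.5 | 0.171 |
| Share 100%, RR 0.6 | 0.729 | 8.3 | 0.206 |

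The fall in AUC runs from about 0.01 to about 0.07, towards no association. At its largest it is about a third of the confidence interval half-width (0.071/0.206 = 0.34). The table shows what leakage could do if it occurred; it does not estimate what will occur.

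**The case against.** The strongest reply is that the article describes no leak. The documentation sentence sets an earliest time, not an immediate release, and it does not say where the reading goes. The Data management plan has study data captured first on a paper CRF and then transcribed to a password-protected database, so documentation may simply mean entry in the research record. Clinicians also have no rule to act on: the article says there are no published CSI data in this population, and both the cut-off and the choice among first, average, median or lowest reading are still to be settled. This is an exploratory cohort whose sampling uncertainty exceeds the illustrated bias. All of that stands, and it limits the point to what could happen.

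Three stronger readings are tempting and are not supported:
- **That the association is contaminated.** The article does not say that clinicians receive or act on CSI.
- **That classification inflates the association.** The outcome definition is fixed and outcomes come from hospital records. No text gives the classifier access to CSI, and the direction of any effect is unknown.
- **That the operator is unmasked because "The result is represented by the CSI shown on the control unit".** This is a general description of the device. The specific rule says the clinician is blinded, and how the display is concealed is operational detail that a condensed article may omit.

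The reply does not remove the stated rule. The article gives a period of masking, and observing it exactly still leaves earlier readings open to be known during later care. Wide confidence intervals do not answer this either, because they report imprecision and would not reveal leakage.

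**Conclusion.** The point holds as a possibility created by the rule as written. Masking covers only the time of each visit, while the CSI-gestation association, the ROC/AUC and the cut-off all depend on what happens between that visit and the birth. The size of any bias cannot be estimated from the document, and it is zero if nobody sees or acts on CSI. On the assumed values above, the treatment route alone would lower the AUC by about 0.01 to 0.07; the CL-measurement and classification routes were not quantified. This is a worthwhile correction of modest weight, because the study is an exploratory feasibility cohort. The verdict rests on the article alone; a longer masking period in the full protocol would resolve it.

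**What to change.** Change the rule under Cervical stiffness assessment so that CSI values stay masked to participants, treating clinicians and whoever classifies the birth as spontaneous or iatrogenic until the delivery outcome is recorded. State that readings are held only in the research record (CRF and REDCap) and not in clinical notes. Log any unmasking as a protocol deviation; deviations are already counted as a feasibility outcome, so no new measure is needed.

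The article puts the end of recruitment at October 2024, so many readings may already have been handled under the current rule. For completed visits, report who had access to CSI values and when, so that readers can judge whether leakage was possible.

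The cost is one amended rule and some restriction on who handles the CRF. No extra staff should be required, provided existing study staff who do not make care decisions can hold the readings.
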